**Methods:**

We will test the hypothesis that topical natamycin 5% in combination with chlorhexidine 0.2% is superior to topical natamycin 5% alone in a two-arm, single-masked RCT (ISRCTN, ISRCTN87195453, registered 27/08/2020,
https://www.isrctn.com/ISRCTN87195453). Participants are adults with FK presenting to tertiary ophthalmic hospitals in Tanzania and Uganda. Baseline assessment includes history, examination, photography, in vivo confocal microscopy and corneal scrapes for microbiology. Participants will be randomised to alternative topical antifungal treatments (topical chlorhexidine 0.2% and topical natamycin 5%; 1:1 ratio, 2-6 random block size). Patients will be reviewed at days 2, 7 (with re-culture), 14, 21, month 2, and month 3. The primary outcome is best spectacle corrected visual acuity (BSCVA) at three months. Primary analysis (intention-to-treat) will be by linear regression, with treatment arm and baseline BSCVA pre-specified covariates. Secondary outcomes include epithelial healing time, scar/infiltrate size, ulcer depth, hypopyon size, perforation and/or therapeutic penetrating keratoplasty, and positive re-culture rate.

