### Randomisation and masking

**
*Sequence generation:*
**

A computer-generated randomisation list will be created by an independent statistician at LSHTM. This statistician will maintain the sequence but will not be masked and will not participate in any other aspect of the study.The allocation ratio will be 1:1 for chlorhexidine + natamycin to natamycin, with blocked randomisation to ensure reasonable balance across different locations over time. Block sizes will randomly vary between 2, 4, and 6.Separate randomisation sequences will be generated for each of the two recruitment centres (Uganda and Tanzania).

**
*Allocation concealment and implementation:*
**

Randomisation sequences will be concealed in sequentially numbered, opaque envelopes.An independent administrator, experienced in trial procedures, will prepare the envelopes and will not be involved in other trial aspects.A research nurse in each centre will open the envelopes sequentially and allocate treatment to participants.The randomisation administrator will be a nurse or pharmacist with appropriate training.Investigational products will be stored in a dedicated, locked drug cabinet in the trial coordination office, managed only by the randomisation administrator.Storage conditions specified by the manufacturer will be adhered to.The randomisation administrator will handle storage, transportation, and dispensing of drugs.Stock reconciliation will be conducted at the end of each recruitment day.

**
*Masking:*
**

Due to differing appearances of the treatments, participants cannot be masked.Clinicians assessing patients will be masked to allocation.The primary analysis statistician will be masked to allocation until the analysis code is pre-tested.Optometrists assessing visual acuity at three months will be masked to allocation.Independent masked grading of photographs will confirm outcome measures and detect any potential bias from clinical examiners.

**
*Unmasking:*
**

Unmasking will only occur if necessary for participant safety.Staff unmasked for data and safety monitoring committee analyses will not participate in other study aspects.A list of unmasked staff will be maintained and approved by the Chief Investigator.Unmasked staff must acknowledge their confidentiality responsibilities in writing.Processes for providing access to unmasked treatment codes and reports will be documented.

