### Sample size considerations

The study is designed to test the hypothesis that natamycin combined with chlorhexidine is superior to natamycin alone in improving the primary outcome (BSCVA at 3 months). Assuming a BSCVA of 0.5 logMAR in the natamycin-only group, a standard deviation of 0.62 in both groups, and an adjusted alpha of 0.0492 (to accommodate interim analysis using the O’Brien-Fleming method), a sample size of 304 ensures 80% power to detect a 0.2 logMAR improvement. Allowing for a 15% dropout rate, the total target enrollment is 358 participants across both sites. 

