### Analysis plan

An intention-to-treat (ITT) approach will be used, analyzing all data based on the assigned randomisation group, regardless of adherence to the treatment protocol. Analyses will follow CONSORT guidelines for non-inferiority trials
^
35
^, and a flowchart will summarize recruitment, randomisation, and follow-up by treatment arm. Baseline characteristics will also be summarized. Details of the SPIRIT checklist are provided as Extended Data and available online (see Data Availability Statement). 

**
*Primary outcome analysis – unadjusted*
**

The primary outcome (BSCVA at 3 months) will be analyzed using linear regression, including baseline BSCVA and treatment arm as covariates. Mixed fungal and bacterial infections identified at baseline will be excluded from the primary analysis. We will use our alpha of 0.0492 to test the null hypotheses at 0.0492 significance. Significance will be assessed using a two-tailed test at 0.0492 level for assessing superiority.

**
*Primary outcome analysis – adjusted*
**

If baseline covariate imbalances occur between treatment arms, adjusted analyses will be conducted to ensure treatment effects are not confounded by these differences. This is particularly important if natamycin + chlorhexidine has a better outcome than natamycin, as the adjusted treatment effects may account for this observed imbalance whilst the unadjusted analyses may not. Sensitivity analyses will allow us to show that any observed positive treatment effect is not solely explained by imbalances at baseline in any of the covariates.

**
*Secondary analyses of the primary outcome*
**

- Per-Protocol Analysis: Re-analysis will be conducted excluding participants with significant deviations, poor adherence (<50%), or mixed/non-fungal infections. 

- Mixed Infections: Secondary analyses will include mixed infections using the same methodology as the primary analysis. 

- Sensitivity Analyses: Missing data will be addressed through multiple imputation or non-random missing data models if necessary. Additional sensitivity analyses will assess outcomes in subgroups such as those with severe vision loss, corneal perforation, or therapeutic keratoplasty. 

**
*Analysis of other determinants for success*
**

Logistic regression models will identify factors associated with poor outcomes (BSCVA >1.0 logMAR), adjusting for trial arm. Multivariate models will refine predictors based on likelihood ratio tests. 

**
*Secondary outcome analysis*
**

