Secondary outcomes listed in
Table 4 will be analyzed using regression models appropriate for the data type, adjusting for any baseline imbalances. 

**Table 4. T4:** Secondary Outcome Measures that will be investigated as part of the trial, together with analysis details.

Secondary outcome measure	Details
Three-week BSCVA	We will analyze the secondary outcome of three-week Best Spectacle-Corrected Visual Acuity (BSCVA) in logMAR using the same methodology applied to the primary analysis of the primary outcome. The three-week BSCVA assessment will include values recorded between 18 days and 5 weeks, with the closest value to 3 weeks being selected.
Presenting VA by Peek	The presenting visual acuity (VA) assessed using Peek Acuity, with and without pinhole, will also be analyzed as a secondary outcome at three months. This measure will be particularly relevant if reliable BSCVA readings cannot be obtained at three months (e.g., if patients do not attend the clinic and at-home visual acuity testing is required). This analysis will follow the same approach as the primary analysis of the primary outcome. A sensitivity analysis, incorporating data from participants lost to follow-up, will use the most recent recorded observation of this variable.
Scar/infiltrate size at 1 week, 3 weeks and 3 months by slit lamp examination.	For scar or infiltrate dimensions, the geometric mean of the two principal axes (in mm) will serve as the outcome variable at one week, three weeks, and three months. The scar size, observed via slit lamp, will be compared between treatment groups at each time point using linear regression. This will include treatment arm and baseline infiltrate/scar size as predefined covariates, controlling for baseline differences.

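### Randomisation is stratified by centre but the primary model has no centre term, which makes the primary test mildly conservative and slightly inefficient, though not invalid

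*Protocol article*

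**What the plan says.** Under Randomisation and masking, allocation is 1:1 with block sizes varying between 2, 4 and 6, and "Separate randomisation sequences will be generated for each of the two recruitment centres (Uganda and Tanzania". Randomisation is therefore stratified by centre.

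The primary model is given twice. The abstract has "Primary analysis (intention-to-treat) will be by linear regression, with treatment arm and baseline BSCVA pre-specified covariates". The Analysis plan has "The primary outcome (BSCVA at 3 months) will be analyzed using linear regression, including baseline BSCVA and treatment arm as covariates". Centre is in neither statement, nor in any other analysis in the Analysis plan or Table 4.

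Two further rules depend on observed balance. For the primary outcome: "If baseline covariate imbalances occur between treatment arms, adjusted analyses will be conducted to ensure treatment effects are not confounded by these differences". For the secondary outcomes in Table 4, these "will be analyzed using regression models appropriate for the data type, adjusting for any baseline imbalances". The article names no candidate covariates and no criterion for imbalance, and does not say which result leads if the adjusted and primary analyses disagree.

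**The concern.** Blocking within centre forces the arms to be nearly balanced in each centre. If centre also predicts the outcome, the treatment difference varies less from trial to trial than a model without centre supposes. Between-centre variance stays in the residual, the reported standard error is too large, and the confidence interval is wider than it needs to be. The trial is planned at 80% power with nothing to spare, so precision that the design has already secured is worth keeping.

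The article gives some reason to think the centres may differ. They serve different populations, see about 900 and 300 microbial keratitis cases a year (Trial setting), and use different mydriatics (Additional topical treatments). None of this shows a difference in three-month vision.

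The second issue is the imbalance trigger. After proper randomisation, baseline imbalance is chance. A model assembled from whatever happens to be unbalanced depends on the data, and it can leave out strong prognostic variables that happen to be balanced.

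**Working it through.** **Inputs from the article.** Sample size considerations gives SD 0.62, target difference 0.2 logMAR, 80% power, 304 evaluable, 15% dropout, 358 enrolled, and an "adjusted alpha of 0.0492 (to accommodate interim analysis using the O’Brien-Fleming method". The test is two-sided (Analysis plan).

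**Assumptions.**
- The larger centre's share is p = 0.75, from 900/(900 + 300). This uses all microbial keratitis cases, not trial recruitment.
- The residual centre difference D in three-month BSCVA runs from 0 to 0.5 logMAR. The article gives no figure.
- The SD of 0.62 includes the centre component.
- Arms are balanced within centre, and the normal approximation applies.

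**Step 1: reproduce the plan.** The critical value for two-sided 0.0492 is 1.967, and the 80% power quantile is 0.842.
- n per arm = 2 × [(1.967 + 0.842) × 0.62 / 0.2]² = 151.6, rounded up to 152, so 304 in total.
- 304 / 0.85 = 357.6, so 358.
- Power at 152 per arm is 80.1% (79.9% with the t distribution).

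Both planned figures reproduce.

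**Step 2: variance due to centre.** Between-centre variance = p(1 − p)D². The within-centre SD is s = √(0.62² − p(1 − p)D²). At D = 0.2 the centre variance is 0.75 × 0.25 × 0.04 = 0.0075, which is 2.0% of 0.3844. At D = 0.5 it is 0.0469, or 12.2%.

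**Step 3: compare the two models.** The model without centre reports SE_m = 0.62 × √(2/152) = 0.0711. The true SE is SE_t = s × √(2/152), and this is also what the model with centre reports. With c = 1.967:
- type I error without centre = 2 × [1 − Φ(c × SE_m / SE_t)]
- power without centre = Φ((0.2 − c × SE_m) / SE_t)
- power with centre = Φ(0.2 / SE_t − c)

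| D (assumed) | Centre share of variance | Type I error without centre | Power without | Power with | Gain, points |
|---|---|---|---|---|---|
| 0 | 0% | 0.0492 | 80.1% | 80.1% | 0 |
| 0.2 | 2.0% | 0.047 | 80.3% | 80.9% | 0.5 |
| 0.3 | 4.4% | 0.044 | 80.6% | 81.8% | 1.2 |
| 0.5 | 12.2% | 0.036 | 81.6% | 85.0% | 3.3 |

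Gains are taken from unrounded values. With a 50:50 split and D = 0.4, type I error is 0.038 and power is 81.4% without centre against 84.2% with it.

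**Step 4: the imbalance trigger.** A null simulation used 304 participants, five covariates explaining 20% or 40% of the variance, and 8,000 runs per setting (Monte Carlo standard error about 0.002). At nominal 0.0492, type I error was:
- 0.045 to 0.049 for the unadjusted model
- 0.040 when adjusting only for significantly unbalanced covariates
- 0.048 to 0.053 when taking the smaller of those two p-values
- 0.046 to 0.051 for all covariates fixed in advance

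**The case against.** The strongest reply is that the effect is small, errs on the safe side and rests on an unsupported assumption. That stands. The article gives no centre difference, and 0.5 logMAR after allowing for baseline BSCVA would be 2.5 times the target effect. Both centres use the same antibiotic and only the manufacturer differs, and caseload is not outcome. At D = 0.2 the standard error shrinks by only about 1%.

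It can also be said that covariate lists and imbalance criteria belong in an analysis plan that is not shown. That holds for the detail of the supplementary analysis. It does not hold for the primary model, whose covariates are stated outright in two places, or for the choice to make adjustment conditional on imbalance.

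A reader might infer four stronger things that the article does not support.
- **That the primary model is chosen after seeing the data.** It is fixed, with its test and alpha. The triggered analysis is a supplementary check. The remark that adjustment matters most when the combination does better is there to challenge a positive result, because the same paragraph aims to show that such a result is not just baseline imbalance.
- **That all secondary models take their covariates from imbalance.** Table 4 fixes covariates for most outcomes: baseline infiltrate or scar size, epithelial defect size, ulcer depth, hypopyon height, organism type, and demographic variables for quality of life. The clause on "adjusting for any baseline imbalances" sits on top of these.
- **That the primary interval is wider than planned.** The sample size uses SD 0.62 with no credit for covariates, and any prognostic value in baseline BSCVA narrows the interval.
- **That the gain should be measured from a fixed 80.1%.** Power without centre also rises as D grows, so the true gain is smaller.

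**Conclusion.** The point holds as a modest matter of efficiency. The stratification factor is missing from a primary model that is otherwise fully stated. Over assumed centre differences of 0.2 to 0.5 logMAR at 75:25, leaving it out costs about 0.5 to 3.3 points of power and makes the test conservative. If the centres do not differ, leaving it out costs nothing. The primary test remains valid and the sample size is unaffected.

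The imbalance trigger is secondary. It touches only the supplementary adjusted analysis and the extra adjustment of secondary outcomes, and the simulation shows no serious inflation of type I error. The objection is that those estimates would come from a model picked by chance imbalance, with no rule for which result leads.

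**What to change.** 1. Add centre (Uganda or Tanzania) as a fixed covariate in the primary linear model, alongside arm and baseline BSCVA.
2. Add centre to the regression models for secondary outcomes where event numbers allow, and stratify the Cox model for time to healing by centre. The exploratory perforation and eye-loss models may have too few events. The Fisher's exact tests and t-tests take no covariates and can stay as they are.
3. Replace the imbalance trigger, for both the primary and the secondary outcomes, with one adjusted sensitivity model run whatever the balance. Choose its prognostic variables before unmasking from those already collected. Baseline infiltrate size and ulcer depth are candidates, but the article gives no evidence that they predict three-month vision beyond baseline BSCVA, so the choice is for the trial team.
4. State that the pre-specified primary model leads if the analyses disagree.

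This needs a few lines of wording and one degree of freedom in the primary model, with no new data and no more participants. Table 5 lists the trial as recruiting, and the article requires protocol changes to be reviewed, so the amendment should go through that route before unmasking.

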### Trial summary

This randomised controlled trial (RCT) adopts a two-stage recruitment process (see
Figure 3), akin to the method previously outlined
^
15,
16
^. All patients presenting with acute microbial keratitis undergo assessment and enrolment into Stage 1 upon providing written, informed consent. This initial stage entails a comprehensive evaluation comprising history-taking, examination, and relevant investigations such as corneal scrapes for microbiological analysis and
*in vivo* confocal microscopy. Should fungal hyphae be evident on smear or confocal microscopy, patients proceed to Stage 2. At this juncture, a trial eligibility assessment is completed, followed by Stage 2 written informed consent. We aim to enrol 358 patients into Stage 2. Eligible individuals with fungal keratitis (FK) are then randomly assigned in a 1:1 ratio to receive either chlorhexidine 0.2% in conjunction with natamycin 5% or natamycin 5% alone as topical ophthalmic treatments. Initially, treatment is administered hourly for the first week, followed by a two-hourly regimen for the subsequent two weeks. Subsequent treatment duration is adjusted based on clinical response. Personnel involved in the study remain blinded to the treatment allocation. Patients are typically admitted initially and undergo follow-up assessments on day-2, day-7 (including re-culture), day-14, day-21, month-2, and month-3. The primary outcome measure is the best spectacle-corrected visual acuity (BSCVA) at three months.

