### Non-pharmacological treatment

Surgical interventions, performed by supervising consultant ophthalmologists, may include bandage contact lens insertion, tissue glue and patch application, or conjunctival flaps to manage small perforations or non-healing ulcers. Corneal transplant is not available in Uganda or Tanzania.

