### Treatment review

At each follow-up appointment, participants will be assessed by an ophthalmic clinician with expertise in fungal keratitis management. Clinical responses to antifungal treatments are generally slower compared to bacterial infections, often necessitating prolonged topical therapy for 4–6 weeks. As a result, adjustments to therapy are typically deferred for at least one week. Additional interventions may be required, including corneal glue application for perforations, conjunctival flap procedures, or therapeutic penetrating keratoplasty (corneal transplantation). 

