Time to full epithelial healing (slit lamp examination by ophthalmic clinician)	The time to re-epithelialization will be calculated as the midpoint between the last review showing an epithelial defect (ED) and the subsequent review where no ED is observed. Fluorescein staining covering an area smaller than 0.5 mm will be considered indicative of a resolved ED, given the challenge of distinguishing smaller defects from pooling in healed areas. Time-to-healing analysis will utilize Cox proportional hazards regression, with treatment group as the primary predictor and baseline ED size (geometric mean in mm) included as a covariate. Survival curves for treatment groups will be plotted using Kaplan-Meier analysis up to the three-month endpoint. The proportional hazards assumption will be tested by stratifying baseline ED size into quartiles. If this assumption is not met, stratified results will be reported. Treatment failure (defined as an ED larger than 0.5 mm at the three-month review) will be compared between groups using Fisher’s exact test.
Rate of healing	The rate of ulcer size reduction will be evaluated by measuring changes in ED size over time intervals (1 week to 3 weeks, and 3 weeks to 3 months) and dividing by the number of days, producing a rate (mm/day). This will be analyzed using Cox regression.
Microbiological cure	For patients with persistent corneal ulcers (defined by ED presence) at day 7, a repeat corneal scrape and microbiological tests will be conducted. Microbiological cure at day 7 will be defined as the absence of growth on culture. Cure rates will be compared between treatment arms using logistic regression, adjusting for organism type (e.g., *Aspergillus spp.*, *Fusarium spp.*, or other).
Ulcer depth at 1 week and 3 weeks (slit lamp examination by ophthalmic clinician).	Depth of corneal ulcers (expressed as a percentage of healthy cornea thickness) will be compared between treatment groups at one week and three weeks. This analysis will adjust for baseline ulcer depth using linear regression.
Hypopyon height at 1 and 3 weeks, (slit lamp examination by ophthalmic clinician)	Hypopyon height (in mm) at one and three weeks will be compared between groups, adjusting for baseline height using linear regression.

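### The treatment-failure and healing-time rules misclassify or drop removed and flap-covered eyes, and perforation and keratoplasty subgroups cannot serve as sensitivity analyses

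*Protocol article*

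**What the plan says.** All references are to the protocol article.

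- **Failure (Table 4, time to full epithelial healing).** The rule is "Treatment failure (defined as an ED larger than 0.5 mm at the three-month review"), compared by Fisher's exact test.
- **Healing time (same row).** Healing is dated to the midpoint between the last review with an epithelial defect and the next review without one. It is analysed by Cox regression with Kaplan-Meier curves to three months.
- **Sensitivity analyses (Analysis plan, secondary analyses of the primary outcome).** "Additional sensitivity analyses will assess outcomes in subgroups such as those with severe vision loss, corneal perforation, or therapeutic keratoplasty". The sentence gives no time point for these states and no model.
- **The same events as outcomes (Table 4).** Perforation, keratoplasty or conjunctival advancement by three months forms one secondary outcome and loss of the eye another. Each has a logistic comparison between arms.
- **Surgery.** The section on non-pharmacological treatment allows conjunctival flaps and then states: "Corneal transplant is not available in Uganda or Tanzania". The treatment review section lists, among interventions that may be needed, "therapeutic penetrating keratoplasty (corneal transplantation").
- **Primary outcome.** "The primary outcome measure is the best spectacle-corrected visual acuity (BSCVA) at three months". The analysis is intention-to-treat apart from mixed infections, and vision of counting fingers or worse is given a logMAR value.

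**The concern.** Both rules need a cornea that can be inspected. An eviscerated or enucleated eye has none, and a flap can hide it. The failure definition has no category for such an eye, and the healing rule asks only whether a defect is seen. The worst result of the disease can thus be recorded as something other than failure in the two comparisons meant to describe healing. If the arms differ in how often eyes are removed or flapped, these comparisons lose that difference, whether it is a benefit or a harm.

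The subgroup sentence raises a second problem. A sensitivity analysis should ask the primary question again under different assumptions. Eyes that perforate or are grafted during follow-up are selected by something treatment may change, so the arms within that group are no longer balanced by randomisation.

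**Working it through.** **1. The plan's own figure.** Inputs from the sample size section: "Assuming a BSCVA of 0.5 logMAR in the natamycin-only group, a standard deviation of 0.62 in both groups", a difference of 0.2, 80% power and "an adjusted alpha of 0.0492" (two-sided, from the Analysis plan). Per arm, n = 2 × (1.967 + 0.842)² × 0.62² / 0.2² = 151.7, so 152 per arm and 304 in total. With 15% dropout, 304 / 0.85 = 357.6, so 358. Both figures reproduce. Nothing below changes them.

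**2. When the events arise.** Table 1 excludes, at Stage 2, previous keratoplasty in the affected eye and ulcers severe enough to need evisceration or a flap at once. In a randomised eye, keratoplasty is therefore a follow-up event, and removal and flaps are expected to be too. Perforation at presentation is not excluded, and severe vision loss could be a baseline state. Those two subgroups may be partly pre-randomisation.

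**3. The failure rule applied literally.** The documents give no removal rate, so these inputs are assumed: 152 eyes per arm and 15 persistent defects in each arm. Removed eyes vary (natamycin alone v combination).

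| Removed | Dropped | Counted as not failed | Counted as failed |
|---|---|---|---|
| 15 v 5 | 15/137 v 15/147 = 10.9% v 10.2%, p = 0.85 | 15/152 in each arm, p = 1.00 | 30/152 v 20/152 = 19.7% v 13.2%, p = 0.16 |
| 12 v 4 | 15/140 v 15/148 = 10.7% v 10.1%, p = 1.00 | 15/152 in each arm, p = 1.00 | 27/152 v 19/152 = 17.8% v 12.5%, p = 0.26 |
| 8 v 8 | 15/144 in each arm, p = 1.00 | 15/152 in each arm, p = 1.00 | 23/152 in each arm, p = 1.00 |

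The coding decides whether a gap appears at all. With equal removals it does not matter.

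**4. The subgroup comparison.** Assumed: 25% perforation on natamycin alone (the introduction's figure of about 25% covers perforation and vision loss together), SD 0.62, and correlation 0.49 between perforation tendency and acuity. Let p be the perforation rate in an arm, and φ the normal density at the cut-point that gives p. Mean acuity among perforated eyes is then shifted by 0.49 × 0.62 × φ/p = 0.304 × φ/p. The ratio φ/p is 1.271 at 25%, 1.400 at 20% and 1.554 at 15%.

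- True difference 0, combination at 20%: 0.304 × (1.400 − 1.271) = +0.04 logMAR within perforated eyes.
- True difference 0, combination at 15%: 0.304 × (1.554 − 1.271) = +0.09, wrongly against the combination.
- True difference −0.20: the perforated subgroup shows −0.16 and −0.11 respectively.
- Equal perforation rates: no distortion (0.00 or −0.20).

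Simulation of the same model gave the same values. The comparison of all randomised eyes stayed at 0.00 or −0.20 throughout.

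**5. Keratoplasty.** One section says transplantation is unavailable in both countries. The treatment review, the subgroup sentence and Table 4 all provide for it. If the first statement holds, the keratoplasty subgroup may be empty.

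**The case against.** The strongest reply is that little turns on this. A reader might infer that the worst outcomes fall out of the randomised comparison. The article does not support that. The intention-to-treat primary analysis stays, very poor vision is given a logMAR value, and perforation or keratoplasty and loss of the eye are each compared by arm. The subgroup analyses are additional and replace nothing. This part of the reply stands. One small gap remains: the primary-outcome section does not name removed eyes, although including them under counting fingers or worse is a reasonable reading.

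It can also be said that the subgroup sentence is condensed. It does not state that arms are compared, so a descriptive reading is open, and a fuller analysis plan may settle it. That limits the point to how the results are labelled and used. The sentence does present them as sensitivity analyses of the primary outcome, and they cannot do that job where the event follows randomisation.

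On the failure rule, coding detail may be left to an analysis plan. But the article states a complete definition, and applied as written it cannot class a removed eye as failed. That is a rule giving a wrong answer, not an omitted detail.

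Finally, giving every perforated or flapped eye a fixed poor acuity would overwrite real measurements, since some of these eyes may keep measurable vision. That objection is right, and the change proposed below avoids it.

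**Conclusion.** The point holds for two secondary comparisons and for the role given to the subgroup analyses. The failure and healing-time rules misclassify or drop removed eyes and corneas hidden by a flap. Any arm comparison within perforation or keratoplasty groups formed after randomisation is not a randomised comparison.

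The size cannot be taken from the article. Under the assumed counts, the failure difference moves from 0.7 percentage points (10.9 − 10.2) to 6.6 (30/152 − 20/152 = 10/152), without reaching significance, and it vanishes with equal removals. Subgroup distortion of 0.04 to 0.09 logMAR rests on an assumed fall in perforation and an assumed correlation, and is zero if treatment leaves perforation unchanged. Sample size and primary inference are untouched.

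**What to change.** 1. **Failure.** Count as a treatment failure any eye with a defect above 0.5 mm at three months, any eye removed by three months, and any cornea that cannot be assessed because of a flap or graft. Show each component by arm.
2. **Healing time.** In the Cox model, keep such eyes as not healed to day 90. Do not score them as healed or censor them at the event.
3. **Subgroups.** Say whether each state is defined at baseline or during follow-up. Label post-randomisation perforation and keratoplasty results descriptive, and do not use them as sensitivity analyses of the treatment effect.
4. **Robustness.** Test it on all randomised eyes, using measured BSCVA wherever it exists. Assign a logMAR value, varied over a stated range, only to eyes with no measurable acuity, such as removed eyes.
5. **Keratoplasty.** Reconcile the statements in non-pharmacological treatment, treatment review, the subgroup sentence and Table 4.

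The cost is a change of wording using data already recorded. The downside is that failure becomes a small composite, which is why its components need to be shown separately.
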